#### Secondary outcomes

(a) Stool frequency: the average daily number of spontaneous defecation recorded in the week before each time-point; (b) stool consistency measured using the Bristol stool scale [33]; (c) quality of life measured using the scale of IBS-quality of life (IBS-QOL) [34]; (d) anxiety measured using the self-rating anxiety scale (SAS) [35]; (e) depression measured using the self-rating depression scale (SDS) [36]; (f) the safety using TXYF and placebo, which will be evaluated in the following aspects: (1) routine examination (blood routine, urine routine, stool routine + occult blood (OB)); (2) biochemical indexes including liver function (aspartate aminotransferase (AST) and alanine aminotransferase (ALT)), kidney function (blood urea nitrogen (BUN), creatinine); (3) heart electrical activity measured using electrocardiogram; (4) adverse events, such as rash, constipation, or other special symptoms, recorded at any time during the treatment by the patient: incidence of adverse events = (number of adverse events/total cases) × 100%; (5) severe adverse events, such as loss of function or disability, life-threatening or even death, recorded at any time during the treatment by the researchers: incidence of severe adverse events = (number of severe adverse events/total cases) × 100%.

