**Methods/design:**

A randomized, multiple-blind, placebo-controlled trial will be conducted. It will consist of an 8-week intervention followed by a 3-month follow-up period.

The target sample size is 96 IBS-D patients aged 18 to 65 years. The eligible participants will be randomly allocated to either TXYF or placebo group in a ratio of 1:1. Participants in the experimental group will take TXYF granules, while participants in the control group will be given TXYF placebo granules. The primary outcome will be the degree of IBS symptom severity measured using the scale of IBS symptom severity score. The secondary outcomes include: (a) stool frequency, and (b) stool consistency measured using the Bristol stool scale, (c) quality of life measured using the scale of IBS-quality of life, (d) anxiety measured using the self-rating anxiety scale, (e) depression measured by the self-rating depression scale, and (f) the safety of using TXYF and placebo. Safety monitoring and assessment will be undertaken throughout treatment.

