## Methods/design

### Study design

This is a randomized, multiple-blind, placebo-controlled superiority trial, and the protocol for this trial has been prepared following the Standard Protocol Items: Recommendations for Interventional Trials (SPIRIT) guidelines (see Additional file 1) [25]. The eligible participants will be allocated randomly into the experimental or placebo control group in a ratio of 1:1. Both groups will have an 8-week intervention followed by a 3-month follow-up period. This trial protocol has been registered in the ISRCTN registry (Reference number: ISRCTN12453166) on the 23 March 2021. A flow diagram of the trial is shown in Fig. 1.

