### Data collection and management

Data collection will be performed during the treatment period, as well as the follow-up period. The data will be recorded in the CRF and entered into an electronic data management software (e.g., EpiData Software). All private and sensitive data (e.g., identification information from participants) will be coded.

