#### Statistical description and statistical analysis methods

With regard to continuous outcomes, Q-Q plots will be used to evaluate normality assumptions. Continuous outcomes conforming to the normal distribution will be presented as mean ± standard deviation (SD) and non-conforming to the normal distribution will be presented as median and interquartile range (IQR) [41]. For both primary continuous outcomes and secondary continuous outcomes, simple or multiple linear regression will be applied to estimate the difference between TXYF group and placebo group. Two preadjusted analyses will be conducted, if appropriate. The first preadjusted regression analysis included only baseline variables (e.g., age, gender, smoking and drinking). The second preadjusted analysis will also adjust for concomitant treatment, a variable thought to be associated with outcome but not affected by treatment allocation.

Categorical data will be expressed by the number and percentage of occurrences. For primary and secondary categorical outcomes, differences will be compared using chi-squared tests and, if appropriate and necessary, logistic regression. The preadjusted analyses will be conducted that adjust for the same covariates as those described for the continuous outcomes.

Estimates of treatment effect will be reported with 95% confidence intervals. Two-tailed *P*-values ≤ 0.05 will be considered statistically significant.

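### Adverse-event incidence is defined as events divided by patients, so repeat events inflate it, and a chi-squared comparison of that ratio would be too liberal

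*Protocol article*

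**What the plan says.** Safety is secondary outcome (f). Under Secondary outcomes, the protocol article gives two formulas, each ending in a percent sign:

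- "incidence of adverse events = (number of adverse events/total cases) × 100"
- "incidence of severe adverse events = (number of severe adverse events/total cases) × 100"

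Neither comes with a rule that a participant counts once.

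The section on statistical description and analysis methods gives a general rule: "For primary and secondary categorical outcomes, differences will be compared using chi-squared tests", with logistic regression where appropriate, at a two-sided 0.05 level. It does not mention adverse events and gives no other method for them. Principle of analysis assigns the safety evaluation to the safety set.

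On timing, adverse events are "recorded at any time during the treatment by the patient" and severe adverse events "recorded at any time during the treatment by the researchers". The abstract says "Safety monitoring and assessment will be undertaken throughout treatment". Study design describes an "8-week intervention followed by a 3-month follow-up period", and Data collection and management says "Data collection will be performed during the treatment period, as well as the follow-up period", without naming adverse events.

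**The concern.** The numerator counts events and the denominator counts patients, yet the result is called an incidence and expressed as a percentage. A reader of the trial report would take it as the share of patients affected. It equals that share only if nobody has more than one event. The article's own examples, rash and constipation, can recur over eight weeks, and one patient can have several different events.

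Chi-squared and logistic methods need one independent yes/no outcome per patient. Events clustered within patients vary more than a binomial count allows, so the test would declare differences too often. Safety is half of the trial's stated aim, so this would affect a headline result, though not the primary outcome.

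A smaller question is which period the adverse-event figures cover.

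**Working it through.** **Inputs from the article.** The event-over-patient formula (Secondary outcomes), 48 per group (Sample size), and the two-sided 0.05 level. The article states no adverse-event rate, so there is no figure of its own to reproduce.

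**Assumed inputs.** Identical arms; a share f of patients affected, 10% to 30%; a mean of m events per affected patient, 1 to 3, generated as 1 + Poisson(m − 1).

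**Step 1: the ratio itself.** With 12 of 48 patients having two events each:

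- as defined: (12 × 2)/48 = 24/48 = 50%
- patients affected: 12/48 = 25%

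**Step 2: one comparison.** Six patients are affected in each arm, with 15 events in one arm and 6 in the other.

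- By events: 15/48 = 31.3% v 6/48 = 12.5%. The pooled proportion is 21/96 = 0.219. Chi-squared = (0.1875)² / [0.219 × 0.781 × 2/48] = 4.94, p = 0.026.
- By patients: 6/48 v 6/48, p = 1.0.

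**Step 3: why the test is too liberal.** The per-patient variance of the event count is f(m² + m − 1) − (fm)². The chi-squared test assumes fm(1 − fm).

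- f = 0.25, m = 2: 0.25 × 5 − 0.25 = 1.00, against 0.5 × 0.5 = 0.25. The ratio is 4, so the critical value 1.96 acts as 1.96/√4 = 0.98, and type I error is about 33%.
- m = 1: the variance is f − f², exactly the binomial value, so there is no excess.

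**Step 4: simulation.** 200,000 null trials per setting, 48 per arm, Pearson chi-squared. Rejection rates for event counts are taken among trials in which neither arm has more events than patients, because otherwise no 2×2 table exists.

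| Mean events per affected patient | 10% affected | 20% affected | 30% affected |
|---|---|---|---|
| 1 | 5.9% | 5.2% | 5.2% |
| 1.5 | 17.6% | 18.9% | 21.9% |
| 2 | 26.0% | 30.2% | 37.2% |
| 3 | 38.7% | 46.9% | 48.1% |

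Counting patients with at least one event gives 5.1% to 5.9% in every setting. With 43 per arm (48 less 10% loss) the results barely move: 30.5% instead of 30.2% at 20% affected and m = 2.

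The ratio passes 100% in at least one arm in about 1.4% of trials at 30% affected and m = 2, and in about 52% at 30% and m = 3.

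**Step 5: the recording window.** Secondary outcomes and the abstract word adverse-event recording and safety monitoring as covering treatment. Data collection and management has data collected in follow-up too. The schedule in Table 1 is not visible in the text available, so the two statements cannot be reconciled from here.

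**The case against.** **The numerator may be loose wording.** The authors may have meant patients with an event. That is possible, but under Primary outcomes the same article builds the response rate from counts of participants and says so. An analyst following the safety formula would count events. Even on the generous reading the sentence needs the same correction.

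**No test of adverse events is named.** This stands in part. The chi-squared link is inferred from the general rule for secondary categorical outcomes, and analysis detail is deferred to a statistical analysis plan not shown here. The inflated type I error is therefore conditional: patients must have repeat events, and event counts must be put in the 2×2 table. The mislabelled percentage does not depend on that inference.

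**The size rests on assumed rates.** This also stands. At one event per affected patient the two definitions coincide. One or two patients with recurrent events would also not normally create a significant difference. With six affected per arm, one patient having three events gives 8 v 6 (p about 0.56), and two such patients give 10 v 6 (p about 0.27). Severe events are less likely to repeat within a patient, so the practical effect there is probably smaller.

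**Recording beyond treatment is not ruled out.** A reader might infer that adverse-event recording stops when treatment ends and that late liver-test changes would be missed. The article does not support either. No section says that recording stops, general data collection continues in follow-up, and Table 1 is not visible. The treatment-period wording attaches to adverse and severe adverse events, not to the liver and kidney tests, which are listed separately.

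**Conclusion.** The definition is wrong as written for both adverse and severe adverse events: it is an events-per-patient ratio presented as a percentage incidence. That conclusion needs no assumption about rates.

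The consequence for a between-group test is conditional on event counts being compared by the categorical methods. Given that, with identical arms of 48 and 10–30% of patients affected, type I error is about 5–6% at one event per affected patient, 18–22% at a mean of 1.5, and 26–37% at 2. It would be too strong to say that the planned safety test is invalid as a matter of fact.

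On timing, the supportable point is only that the stated window is unclear across sections. The primary outcome is unaffected. The correction should be made because it concerns a main safety figure and is easy.

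**What to change.** Redefine both incidences as the number of participants with at least one adverse event (or severe adverse event) divided by the number of participants in the safety set. Use these for any comparison between groups. Report the numbers of events separately, as description.

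Reconcile the wording under Secondary outcomes and in the abstract with Data collection and management and with Table 1, and state the adverse-event recording window once.

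The cost is a few sentences in the protocol or analysis plan. The participant-level count needs no new data, provided each recorded event is linked to its participant.

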#### Patient timelines for participants

The schedule of enrolment, treatment and assessments is presented in Table 1.

**Table 1 Tab1:**
[figure not shown]
Schedule of enrollment, treatment and outcome assessment

*TXYF* Tongxie Yaofang Granules, *IBS-SSS* irritable bowel syndromes symptom severity score

Routine examination including blood routine, urine routine, stool routine, and occult blood test (OBT); biochemical indexes including liver function (aspartate aminotransferase (AST) and alanine aminotransferase (ALT)) and kidney function (blood urea nitrogen (BUN), creatinine)

### Sample size

According to previous studies [37], it is estimated that TXYF can produce efficacy response (according to IBS-SSS) in 73% of participants with eight weeks treatment. Under the same treatment duration and evaluation criteria used in this trial, no results of placebo treatment of IBS-D were found. However, based on previously published relevant studies [38, 39], we expect TXYF to have a 30% higher response rate than placebo in the primary outcome, and superiority margin is expected to be 10% (*δ* = 10%). The ratio of the TXYF group to the control group was 1:1. So, the total sample size of 96 is based on the following formula [40], when *α* = 0.05, power = 0.8, and the estimated loss of participants is 10% [31]. That is, the number of participants to be enrolled in the trial should be 48 in each group.
$$ n={\left({Z}_{1\hbox{-} \alpha / 2}+{Z}_{1\hbox{-} \beta}\right)}^2\left[{P}_1\left( 1\hbox{-} {P}_1\right)+{P}_2\left( 1\hbox{-} {P}_2\right)\right]/{\left(P 1\hbox{-} P 2\hbox{-} \delta \right)}^2 $$

Where *n* denotes the sample size of each group, the value of *Z*_*1-α*_ and *Z*_*1-β*_ needs to consult the Z value table, *P*_*1*_ denotes the rate of the experimental group and *P*_*2*_ represents the rate of the control group, and *δ* represents the superiority margin. Therefore, when calculating the sample size of this trial, the value of *Z*_*1-α*_ is 1.96, the value of *Z*_*1-β*_ is 0.842, the value of *P*_*1*_ is 73%, the value of *P*_*2*_ is 43%, and the value of ***δ*** is 10%.

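### The stated formula needs 87 evaluable patients per group (96–97 with loss), but 96 is used as the total, so power for the 10% margin is about 50–58%, not 80%

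*Protocol article*

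**What the plan says.** The Sample size section assumes, from earlier work, that "TXYF can produce efficacy response (according to IBS-SSS) in 73% of participants with eight weeks treatment". It expects placebo to be 30 points lower (43%), sets a superiority margin of 10 points, and uses 1:1 allocation, alpha 0.05 and "power = 0.8, and the estimated loss of participants is 10" percent. It prints a formula in which n "denotes the sample size of each group", and lists the values to be entered: 1.96, 0.842, 73%, 43% and 10%.

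It then states that "the total sample size of 96 is based on the following formula" and that "the number of participants to be enrolled in the trial should be 48 in each group". The Abstract repeats the figure ("The target sample size is 96 IBS-D patients"), and so does the Trial setting section.

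The section on statistical description and analysis methods plans chi-squared tests, with logistic regression where needed, for categorical outcomes. Its decision rule is "Two-tailed *P*-values ≤ 0.05 will be considered statistically significant". It mentions no margin.

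**The concern.** A formula that returns the size of one group should not lead to a total of 96 unless it returns about 48 after loss, or about 43 before it. A 10-point margin reduces the effect to be shown from 30 points to 20. Because n varies with the inverse square of that effect, the margin multiplies the requirement by (30/20)² = 2.25, and 43 evaluable per group looks far too few.

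The stake is the claim of 80% power for the primary response rate. A reader of this section would take 96 patients as enough to show that the herbal formula beats placebo by more than 10 points. If the arithmetic is wrong, a result that misses the margin would be read as evidence against the treatment when the trial had little better than an even chance of meeting it under its own assumptions.

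**Working it through.** **Inputs**, all from the Sample size section: P1 = 0.73, P2 = 0.43, δ = 0.10, Z values 1.96 and 0.842, loss 10%, allocation 1:1, n per group.

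**1. The protocol's formula with its own inputs**

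- Variance term: 0.73 × 0.27 + 0.43 × 0.57 = 0.1971 + 0.2451 = 0.4422
- Squared sum of Z values: (1.96 + 0.842)² = 2.802² = 7.851
- Effect beyond the margin: 0.73 − 0.43 − 0.10 = 0.20, squared 0.04
- n = 7.851 × 0.4422 / 0.04 = 86.8, so **87 per group** (174 in total)

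**2. Allowance for 10% loss**

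- 87 × 1.1 = 95.7, so 96 per group (192 in total)
- 87 / 0.9 = 96.7, so 97 per group (194 in total)

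The number 96 is reproduced exactly, but as the enrolled size of one group. The protocol uses it as the total and halves it.

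**3. Other readings that might give 48 per group**

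| Reading | Per group | With 10% loss |
|---|---|---|
| Margin 10%, one-sided 0.05 | 69 | 76–77 |
| Margin 10%, 30% taken as a relative difference | 248 or more | larger still |
| No margin, unpooled variance | 39 | 43–44 |
| No margin, pooled variance | 42 | 47 |
| No margin, pooled, continuity correction | 48 | 53–54 |

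No reading that keeps the margin comes near 48. The closest match, 47 per group (94 in total), drops the margin and uses a formula the protocol does not print.

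**4. Power of the planned size against the 10-point margin**

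Power = Φ(0.20 / √(0.4422/n) − 1.96)

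- n = 48: √(0.4422/48) = 0.0960; 0.20/0.0960 = 2.084; Φ(0.124) = **54.9%**
- n = 43 (48 × 0.9 = 43.2): √(0.4422/43) = 0.1014; 0.20/0.1014 = 1.972; Φ(0.012) = **50.5%**

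Exact enumeration of the unpooled Wald test gives 58.1% at 48, 51.6% at 44 and 54.1% at 43. The uneven pattern comes from the discreteness of the binomial counts.

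**5. Difference needed for 80% power against the margin**

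Solving (d − 0.10) / √(variance/n) = 2.802 for the true difference d:

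- n = 48: 35.9 points with placebo held at 43%, or 36.5 points with the herbal arm held at 73%
- n = 43: 37.2 or 37.9 points on the same two assumptions

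The planning difference is 30 points.

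**6. Same rates, two-sided test of no difference (δ = 0)**

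- n = 7.851 × 0.4422 / 0.09 = 38.6, so 39 per group; 39/0.9 = 43.3, so 44 enrolled
- Power at 43: 81.6% (pooled) to 84.1% (unpooled)
- Power at 48: 85.7% (pooled) to 87.8% (unpooled)

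**The case against.** The strongest reply is that the planned analysis does not use the margin. The chi-squared test with a two-tailed 0.05 threshold is a test of no difference, and for that test 48 enrolled per group is adequate: power stays above 80% even after 10% loss. On this view the patients are sufficient and only the justification is wrong.

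This stands as far as it goes. It limits the consequence: the planned chi-squared test is not shown to be underpowered, and the low figures apply only to the 10-point margin claim for the response rate. They also say nothing about the comparison of post-treatment IBS-SSS scores, which the Primary outcomes section names as well. But it does not rescue the text, which derives 96 from the margin and claims 80% power on that basis. It also exposes a second mismatch, since the sample size is built on a hypothesis that the analysis section never tests.

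Two smaller cautions are fair. That the per-group 96 was mistaken for a total is an inference from the matching number, because the protocol does not show its steps. And the shortfall in power is 25–30 points by the normal approximation but about 22–26 points on the exact figures.

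An unseen full protocol or analysis plan does not change the finding. The article prints a complete calculation whose result does not follow from it.

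**Conclusion.** The concern holds. The formula, its inputs, the per-group definition of n and a total of 96 cannot all stand. The stated calculation requires 87 evaluable per group, or 192–194 patients enrolled with 10% loss, about twice the stated total.

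For the hypothesis as stated, power is about 50–55% by the protocol's own approximation and 54–58% by exact enumeration, at 43 to 48 evaluable per group. These figures assume that the response rates really are 73% and 43% and that loss is no more than 10%. For a plain two-sided comparison at the same rates, 48 enrolled per group gives about 82–84% power after loss and 86–88% without it.

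This must be corrected: the power claim for the primary response rate is wrong for the hypothesis on which the protocol bases it.

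**What to change.** Rewrite the Sample size section without changing enrolment:

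1. State that the formula with the 10-point margin gives 87 evaluable per group (97 enrolled, dividing by 0.9), and that 48 enrolled per group has about 50–55% power for that hypothesis (54–58% exact).
2. Base the justification for 48 per group on a two-sided test of no difference, which is what the analysis section plans: 73% v 43%, alpha 0.05, 48 enrolled and 43 evaluable per group, power about 82%.
3. Say openly that this justification replaces the margin-based one and was adopted after recruitment began. Settle it before unblinding, so that dropping the margin cannot appear to depend on the results. A significant result should then not be reported as superiority by more than 10 points unless the lower confidence limit exceeds 10 points.

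No further patients or data are needed. The cost is revised wording in the protocol and report, a much less favourable power figure for the margin, and the ethics and registry submissions that the Ethics section requires for amendments. If the sponsor prefers to keep the margin with 80% power, the alternative is to enrol about 192–194 patients and to add the margin to the analysis section.

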### Data collection and management

Data collection will be performed during the treatment period, as well as the follow-up period. The data will be recorded in the CRF and entered into an electronic data management software (e.g., EpiData Software). All private and sensitive data (e.g., identification information from participants) will be coded.

### The trial quality control

The regulations for trial quality control are as follows: (a) the designated personnel from FSH-BUCM are responsible for the monitoring of the entire trial and (b) the designated personnel from CEBCM-BUCM assisted in monitoring the entire trial.

The content of quality control includes the following: (a) ensure that the trial process complies with the protocol and ensure the truth, accuracy, and completeness of the data and (b) monitor the progress of the trial, ensure the timely recording and reporting of adverse events, and ensure the informed consent and protection of the participants.

### Statistical analysis

Data analysis will follow the trial statistical analysis plan and be performed by the designated personnel from CEBCM-BUCM. All data will be processed by statistical analyses with SPSS or other appropriate software.

